# Omega-3 mechanism of action in inflammation and endoplasmic reticulum stress in mononuclear cells from overweight non-alcoholic fatty liver disease participants: study protocol for the “Brazilian Omega Study” (BROS)—a randomized controlled trial

**DOI:** 10.1186/s13063-021-05702-x

**Published:** 2021-12-18

**Keywords:** Overweight, GPR120, Omega-3, Inflammation, Endoplasmic reticulum stress, NAFLD

## Abstract

**Abstract:**

The low-grade inflammation is pivotal in obesity and its comorbidities; however, the inflammatory proteins are out of target for traditional drug therapy. Omega-3 (ω3) fatty acids can modulate the downstream signaling of Toll-like receptor (TLR) and tumor necrosis factor-α receptor (TNFα) through GPR120, a G-protein-coupled receptor, a mechanism not yet elucidated in humans. This work aims to investigate if the ω3 supplementation, at a feasible level below the previously recommended level in the literature, is enough to disrupt the inflammation and endoplasmic reticulum stress (ER-stress), and also if in acute treatment (3 h) ω3 can activate the GPR120 in peripheral blood mononuclear cells (PBMC) and leukocytes from overweight non-alcoholic fatty liver disease (NAFLD) participants. The R270H variant of the *Ffar4* (GPR120 gene) will also be explored about molecular responses and blood lipid profiles. A triple-blind, prospective clinical trial will be conducted in overweight men and women, aged 19–75 years, randomized into placebo or supplemented (2.2 g of ω3 [EPA+DHA]) groups for 28 days. For sample calculation, it was considered the variation of TNFα protein and a 40% dropout rate, obtaining 22 individuals in each group. Volunteers will be recruited among patients with NAFLD diagnosis. Anthropometric parameters, food intake, physical activity, total serum lipids, complete fatty acid blood profile, and glycemia will be evaluated pre- and post-supplementation. In the PBMC and neutrophils, the protein content and gene expression of markers related to inflammation (TNFα, MCP1, IL1β, IL6, IL10, JNK, and TAK1), ER-stress (ATF1, ATF6, IRE1, XBP1, CHOP, eIF2α, eIF4, HSP), and ω3 pathway (GPR120, β-arrestin2, Tab1/2, and TAK1) will be evaluated using Western blot and RT-qPCR. Participants will be genotyped for the R270H (rs116454156) variant using the TaqMan assay. It is hypothesized that attenuation of inflammation and ER-stress signaling pathways in overweight and NAFLD participants will be achieved through ω3 supplementation through binding to the GPR120 receptor.

**Trial registration:**

ClinicalTrials.gov #RBR-7x8tbx. Registered on May 10, 2018, with the Brazilian Registry of Clinical Trials.

**Supplementary Information:**

The online version contains supplementary material available at 10.1186/s13063-021-05702-x.

## Background

The world is losing the war against obesity [1], a phenomenon endorsed by ineffective therapeutic drugs or unsuccessful weight loss maintenance after bariatric surgery [2]. It is well recognized that excess saturated fatty acids from ultra-processed foods, de novo lipogenesis, and visceral adipose tissue efflux can activate and intensify pro-inflammatory signaling and endoplasmic reticulum stress response (ER-stress) while reducing systemic insulin sensitivity [3–6]. The hyperglycemia-induced by impaired glucose uptake by the skeletal muscle and increased hepatic gluconeogenesis and glycogenolysis [5–9] lead to non-alcoholic fatty liver disease (NAFLD) development, common obesity-associated comorbidity [6].

Monocytes and lymphocytes play a pivotal role in inflammation and may be actively involved in NAFLD development or progression [10, 11]. Leukocytes are sensitized by inflammatory proteins and respond to changes in the levels of the fatty acid by regulating a wide gene network, including those involved in immune response and lipid metabolism [12]. Because NAFLD is directly associated with increased plasma lipid levels, it is possible that data obtained from isolated peripheral blood mononuclear cells (PBMCs) could reflect the in vivo condition and contribute to biological and clinical insights into the human NAFLD process [10, 11]. ER-stress and activation of the unfolded protein response (UPR) have been linked to a variety of inflammatory and stress signaling systems mainly mediated by c-JUN N-terminal-Kinase (JNK) and inositol-requiring enzyme 1α (IRE1α) proteins. Inflammatory and ER-stress signaling in PBMC seems to reflect changes occurring in metabolically active organs such as the adipose tissue, skeletal muscle, and liver [10, 11].

During obesogenesis, the liver can be affected by inflammation triggered by TLR and sustained by cytokines and its receptors such as tumor necrosis factor-alpha (TNFα), interleukins (IL) 1, and IL6 [13–15]. Both intracellular pathways converge to the phosphorylation of TAK1 (TGFβ-activated kinase1), which activates the canonical NFκB pathway [16–18]. Thus, the non-pharmacological approach of omega-3 (ω3) fatty acids emerges as a potential strategy to control the systemic pro-inflammatory tonus once ω3 attenuates the TAK1 activity [4, 17, 19–22].

Since the 1970s, ω3 has been used and evidenced as an anti-inflammatory due to changes in the ω6: ω3 ratio [23, 24]. However, during the 2000s decade (2000–2010), some G-protein-coupled receptor (GPCR) members were identified as possible fatty acids’ receptors. Among them, GPR120 was recognized as ω3 being its major activator [25]. Then, in 2010, a hallmark work of Oh et al. [17] showed the detailed molecular mechanism of ω3 as an anti-inflammatory nutrient. On the cell surface, ω3 fatty acids (eicosapentaenoic—EPA-[C20:5] or docosahexaenoic—DHA-[C22:6]) bind to GPR120, while attracting the intracellular beta-arrestin 2 (βarr2) protein and inhibiting TAK1 phosphorylation in hepatocytes and adipocytes. This mechanism appears to be reinforced when βarr2 also recruits the NLPR3 (NOD-, LRR-, and pyrin domain-containing protein 3) protein, disrupting the inflammasome, a structure involved in the IL1β and IL18 maturation [26]. After GPR120/ω3 internalization induced by βarr2, free ω3 in the cytosol can be derived into pro-resolutive mediators such as resolvins, maresins, and protectins, which are well recognized ω3 subcompounds [27, 28]. The dynamic antiinflammatory pleiotropism orchestrated by ω3 is strengthened when this molecule activates the peroxisome proliferator-activated receptor-gamma (PPARγ), in which it blocks the nuclear translocation of NFkB [18].

Nonetheless, some clinical trials were not able to show any ω3 benefits in human health [29, 30]. Some guidelines for the management of cardiovascular diseases demonstrate weak evidence or do not recommend ω3 fatty acids as weak evidence or without the strength of recommendation [31, 32]. Therefore, we propose an investigation to understand the reason for this “conundrum” in ω3 knowledge. The present study aims to clarify the recognized but not solved biases, commonly found in studies such as [1] uncertified ω3 fatty acid content in capsules or fish’s flesh, [33] [2] uncontrolled bioavailability from gut to the bloodstream and bioaccessibility from the blood to cell incorporation/uptake, [3] ω3 discrepant doses [4], [4] ω3 EPA: DHA blend, [5] incorrect placebo choices [34, 35], and [6] the presence of GPR120 polymorphism [36].

Here, overweight/obese NAFLD patients are chosen in such a way to deviate from cardiovascular studies’ possible biases. Thus, they will be monitored on their inflammatory and ER-stress pathways in PBMCs and neutrophils.

## Subjects and methods

### Study design and settings

This is a triple-blinded (investigators, statistical analysts, and participants), single-centered, randomized placebo-controlled, prospective intervention trial. This protocol is written following the Standard Protocol Items: Recommendations for Interventional Trials (SPIRIT) checklist [37]. The study is designed to investigate the molecular action mechanisms of ω3 as antiinflammatory and anti-ER stress through GPR120 receptor in peripheral blood mononuclear cells (PBMC) and leukocytes of overweight and obese subjects with visceral obesity and non-alcoholic fatty liver disease (NAFLD). The study protocol was approved by the Ethics Committee of the Federal University of Sergipe (#80476517.2.0000.5546) and registered at the Brazilian Registry of Clinical Trials (#RBR-7x8tbx), on May 10, 2018, retrospectively registered: https://ensaiosclinicos.gov.br/rg/RBR-7x8tbx. All outpatients will be informed by study design before signing the informed consent form.

In the first part of the intervention (acute measurement [3 h after the first capsule intake]), the surrogate outcomes will be [1] ω3 fatty acid concentration in bloodstream, [2] association between GPR120 and βarr2 proteins, and [3] ω3 fatty acid concentration into PBMCs. In the second part, after chronic treatment (28 days of supplementation), the primary outcome will be considered the reduction (upper to 10%) in the TNFα and IL6 protein contents in PBMCs. Both parts of the intervention will be carried out in PBMC and leukocytes. Outcomes such as body weight, waist circumference, and glycemia will not be considered due to short supplementation time and study aim.

### Eligibility

Eligibility criteria will be overweight or obese subjects (BMI > 24.9 kg/m [2]), with visceral adiposity (waist circumference > 80 cm for women and > 94 cm for men) [38], the age range of 19–75 years. Outpatients, who were for the first time consulted by an expert physician, from January 2016 to December 2018, at the Hepatology Clinic of the Federal University of Sergipe, Aracaju, Brazil, were diagnosed with non-alcoholic fatty liver disease (NAFLD) using ultrasound and laboratory tests. The exclusion criteria will consider any history of chronic liver diseases, such as viral or drug hepatitis, confirmed Wilson disease, primary hemochromatosis, suffering from hyper or hypothyroidism, cancers, diabetes *mellitus* type 1, diabetes mellitus type 2 in insulin therapy, obesity due to excessive use of corticosteroids, Cushing’s syndrome, patients with chronic infections, autoimmune diseases, in abuse of alcohol, in use of hepatotoxic drugs, pregnant, and breastfeeding women. Additionally, patients who are not able to participate in the standardized anthropometric evaluation in the study, such as patients with amputated limbs and those who cannot answer the questionnaires, such as the ones with neurological diseases, will not be eligible. Patients with acute myocardial infarction and stroke in the last 5 years are precluded from participating. Individuals taking anti-inflammatory drugs and who in the last 3 months before the study made use of nutritional supplements containing oils, fats, or fatty acids will be excluded. Those who had a weight loss of more than 10% of body weight in the last 3 months will also be excluded.

### Sample size calculation

The sample size calculation was carried out using the G * Power 3.1.9.2 software, and the following values and information were considered: [1] two groups (control and treatment) and [2] effect size *d* = 1.15 considering the variation of TNFα/βactin protein observed in the study by Huang et al. (2016) [39]. In this study, the control group showed 0.45±0.04 (average of arbitrary units ± standard deviation) for TNFα while the telmisartan treated group showed 0.36±0.04 [39]. As in the reference study [39], three types of drugs were used (telmisartan, cyclosporine, and 4-aminopyridine), and the least effective was chosen, understanding that eating will have a possible minor effect concerning hypertensive drugs. This procedure may reduce type II error, [3] type I error *α* = 0.05, and [4] sampling power (1 - *β*) = 85% [5]. The sample size needed was 16 individuals in each group. However, considering a 40% dropout rate, it will be selected 22 per group.

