### Randomization

The distribution between groups, placebo or ω3, will be randomly assigned into groups, placebo or ω3. A sequence number will be generated by SPSS 25.0 under the ratio of 1:1. The numbers will be placed in a sealed envelope and randomly distributed to the participants. After, participants will be listed in ascending order based on biochemical and anthropometric variables, grouped in blocks of two, and then allocated to each of the groups in an equalized manner to ensure group homogeneity. All eligible individuals by the users of the selection will receive a unique and non-transferable code. An independent data manager, who is not involved in clinical practice or patient recruitment, will create the randomization sequence.

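### With 40% dropout, 22 per group leaves about 13 completers, not the 16 required, so the stated 85% power is not reached

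*Protocol article*

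**What the plan says.** The sample size section of the protocol article sets out a two-group comparison with "effect size *d* = 1.15 considering the variation of TNFα/βactin protein", "type I error *α* = 0.05" and "sampling power (1 - *β*) = 85" per cent. It then concludes: "The sample size needed was 16 individuals in each group. However, considering a 40% dropout rate, it will be selected 22 per group". The abstract repeats the result as "a 40% dropout rate, obtaining 22 individuals in each group".

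The Recruitment section has 44 consented and assessed people drawn and then randomised, and the Randomization section gives equal allocation ("A sequence number will be generated by SPSS 25.0 under the ratio of 1:1"). So 22 is the number randomised per arm. It is not a screening number from which losses occur before randomisation.

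The primary outcome (Study design and settings) is the TNFα and IL6 protein content of PBMCs after 28 days. The section on data treatment and statistical aspects names Student's t test and the Mann-Whitney U test for the comparison between groups.

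**The concern.** A dropout allowance should ensure that the required number is still there after the assumed loss. The required n is therefore divided by the proportion retained. Here it appears to have been multiplied by one plus the dropout rate. The two operations are close when dropout is small and differ clearly at 40%.

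If so, the trial falls short of its own requirement whenever its own dropout assumption comes true, even if the effect size is right. A null result would then be read as coming from a trial with 85% power when the true figure is lower.

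**Working it through.** **Inputs** (all from the sample size section unless noted): d = 1.15; alpha 0.05, sidedness not stated; target power 85%; 16 per group needed; 40% dropout; 22 per group selected; 1:1 allocation (Randomization section).

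**Step 1: reproduce the 16.** Sample size per group at d = 1.15 and 85% power:

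| Method | n per group |
|---|---|
| Normal approximation, two-sided: 2(1.960 + 1.036)² / 1.15² = 13.6 | 14 |
| t test (noncentral t), two-sided: 14.6 | 15 |
| Mann-Whitney, normal data (efficiency 3/π = 0.955), two-sided: 14.6 / 0.955 = 15.3 | 16 |
| t test, one-sided: 11.6 | 12 |

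The stated 16 is the two-sided Mann-Whitney figure, or the two-sided t-test figure plus one. A one-sided calculation does not give it, so two-sided testing is assumed below.

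**Step 2: the dropout allowance.**

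- Required: 16 / (1 − 0.40) = 26.7, so 27 per group (54 in total).
- Printed: 22. This matches 16 × 1.40 = 22.4 rounded down. The route is an inference.
- Left after 40% loss from 22: 22 × 0.60 = 13.2, about 13, which is 3 short of 16.
- Largest dropout that keeps 16 of 22: (22 − 16) / 22 = 6/22 = 27.3%.
- If each participant drops out independently with probability 0.40, the chance that an arm of 22 keeps at least 16 is 15.8%. The chance that both arms do is 0.158² = 2.5%.

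**Step 3: power with the completers left.** Noncentral t with noncentrality d√(n/2) and 2n − 2 degrees of freedom. For n = 13 the noncentrality is 1.15 × √6.5 = 2.93, with 24 degrees of freedom and critical value 2.064. For Mann-Whitney, n is multiplied by 0.955.

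| Completers per group | t test | Mann-Whitney |
|---|---|---|
| 13 | 80.3% | 78.3% |
| 14 | 83.4% | 81.5% |
| 15 | 86.0% | 84.3% |
| 16 | 88.2% | 86.6% |

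Averaged over binomial dropout in both arms, t-test power is 79.7%. The normal approximation at n = 13 gives 83.5%, which is too optimistic at this size and still below 85%. With 13 per group, the effect detectable with 85% power by t test is d = 1.23, against the planned 1.15.

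**The case against.** The arithmetic is hard to contest, so the case on the other side concerns how much it matters.

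- **The loss is moderate.** The right comparison is with the stated 85%, not with the 88% that 16 per group would give by t test. The shortfall is then about 5 to 7 points, and 80% is still a conventional level. This stands.
- **The 16 has one to spare under the t test.** Fifteen per group is enough for 85% by t test, so the shortfall against the power target is 2 completers and the tolerable dropout is 7/22 = 32%. This also stands, but 15 / 0.6 = 25 is still more than 22, and the assumed 40% exceeds 32%.
- **A one-sided test would keep the power.** With 13 per group it would give 88.6%. But a one-sided test needs only 12 per group and so does not explain the stated 16.
- **The effect size is itself in doubt.** The reference values ("the control group showed 0.45±0.04 (average of arbitrary units ± standard deviation) for TNFα"; "the telmisartan treated group showed 0.36±0.04") give (0.45 − 0.36) / 0.04 = 2.25, not 1.15, and at 2.25 even 13 per group has over 99.9% power. That is a separate inconsistency. The plan chose 1.15, and the dropout step is wrong whatever d is.
- **The repeated-measures analysis may differ in power.** The plan first runs a two-way analysis of variance with time as a repeated factor. If d = 1.15 refers to the raw-score SD, a comparison of changes with 13 per group has 66% power at a pre-post correlation of 0.3, 80% at 0.5, 88% at 0.6 and 95% at 0.7. The article gives no correlation, so this neither rescues the plan nor worsens the finding.
- **Intention to treat.** The article invokes the principle but describes nothing that would recover the information of a participant without a day-28 PBMC sample.

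**Conclusion.** The concern holds. Twenty-two per group cannot supply 16 completers at 40% dropout, by any route: about 13 remain, and 27 would be needed. On the plan's own assumptions power is about 80% (t test) or 78% (Mann-Whitney), against the stated 85%.

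The count of completers needs no assumption beyond the plan's own figures. The power figures rest on d = 1.15, two-sided alpha of 0.05, a simple comparison of the two groups at day 28 and, for Mann-Whitney, normally distributed data. If actual dropout is 27% or less, 16 per group are kept and the shortfall disappears. That 22 was obtained as 16 × 1.4 is likely but inferred, and the conclusion does not depend on it.

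**What to change.** Correct the sample size section and the abstract. There are two ways to do it.

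1. **Keep 44 and restate.** Suggested text: *With 22 per group and 40% dropout, about 13 completers per group are expected, giving about 80% power for d = 1.15 by a two-sided t test at the 5% level (78% by Mann-Whitney test); 16 completers per group are kept only if dropout is 27% or less.* This costs two sentences and a less favourable stated power, with no extra participants. It corrects the claim but does not remove the shortfall.
2. **Keep the 16 completers and randomise 27 per group.** This adds 5 per group, 10 in total (54 instead of 44).

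Under the first option, a baseline-adjusted analysis (ANCOVA) of the day-28 value could recover the loss. Dividing d by √(1 − r²), where r is the correlation between baseline and day 28, with 13 per group and 23 degrees of freedom, power is about 84% at r = 0.3, 90% at r = 0.5 and 98% at r = 0.7. The article does not give r. These values are assumptions, and at r = 0.3 the power is still just under 85%.

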### Recruitment

Patients’ volunteers will be recruited from the Hepatology Clinic via a phone call to interview and screen participants according to inclusion and exclusion criteria. For each participant, there will be a maximum of 10 attempts to make calls upon the first contact asking participants to fill the questionnaire; if he/she cannot fill the questionnaire, another ten attempts to conduct the phone interview will be made. For a participant to be eligible, one has to agree to answer a screening questionnaire based on the Surveillance of Risk Factors and Protection Survey for Chronic Non-Communicable Diseases by Telephone Interviews (Vigitel) [40]. Then, another interview will be scheduled to confirm the data obtained by phone and the nutritionist will explain the study procedures and consent form to the participants. Participants who agree to participate in the study will sign the consent form and go through the initial assessment. Then, 44 individuals will be randomly drawn for participation in the study, and subsequently, they will be randomized into the study groups: placebo and ω3. To maintain confidentiality, each participant will be codified with a number, and only one co-author of the study will have the complete name and data of the participants.

### Assessments to randomization

Before the randomization, an assessment will be made, including a questionnaire about sociodemographic data, alcoholism, smoking, prescription drugs, anthropometric assessment, and body composition (through bioelectric impedance). A blood sample collection will be performed for assessment of plasma glucose levels, insulin, ferritin, glycated hemoglobin, total cholesterol, HDLc and LDLc lipoproteins, triacylglycerol, alanine aminotransferase, aspartate aminotransferase, and C-reactive protein at the Hepatology Clinic.

### Randomization

The distribution between groups, placebo or ω3, will be randomly assigned into groups, placebo or ω3. A sequence number will be generated by SPSS 25.0 under the ratio of 1:1. The numbers will be placed in a sealed envelope and randomly distributed to the participants. After, participants will be listed in ascending order based on biochemical and anthropometric variables, grouped in blocks of two, and then allocated to each of the groups in an equalized manner to ensure group homogeneity. All eligible individuals by the users of the selection will receive a unique and non-transferable code. An independent data manager, who is not involved in clinical practice or patient recruitment, will create the randomization sequence.

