#### Data treatment and statistical aspects

A steering committee will be organized for trial supervision. The process of data collection and management will be monitored by them. The committee may recommend and request the principal investigator to make some changes to the plan. To increase the security and data quality, the records will be inputted at the bank by one person and checked by another one. Data analysis will be performed according to the intention-to-treat principles [56]. The software Statistical Package for Social Sciences (SPSS), v. 22.0, will be used for data entry and analysis. Statistical analysis will be performed through descriptive analysis, with numerical variables expressed as the mean and standard deviation (SD) or median and interquartile range. All data will be subjected to the Shapiro-Wilk normality test. First, a two-way analysis of variance will be performed to check intra- and intergroup differences. Time will be added as a repeated factor, treatment as an independent factor, and the other variables (e.g., anthropometric data, food intake, blood analysis) as covariates.

The paired Student’s *t* test or Wilcoxon’s test will be used to compare the time effects. The Student’s *t* test and Mann-Whitney *U* test will be used to investigate group differences (placebo and treatment). All tests will be considered significative *P*<0.05. After trial completion, the principal investigator (PI) will be responsible for data archiving and preservation. Only investigators can access data. The PI will be responsible to terminate the trial at any moment.

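### Two allocation procedures are described in sequence, they cannot both fix the arm, and no chance element is stated for the last one

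*Protocol article*

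**What the plan says.** The Randomization section of the protocol article makes these statements, in this order:

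- Assignment is random: "The distribution between groups, placebo or ω3, will be randomly assigned into groups, placebo or ω3".
- The tool and ratio are named: "A sequence number will be generated by SPSS 25.0 under the ratio of 1:1".
- The sequence is delivered to participants: "The numbers will be placed in a sealed envelope and randomly distributed to the participants".
- A further step follows: "After, participants will be listed in ascending order based on biochemical and anthropometric variables". Participants are then "grouped in blocks of two, and then allocated to each of the groups in an equalized manner to ensure group homogeneity".
- Responsibility is given for the sequence only: "An independent data manager, who is not involved in clinical practice or patient recruitment, will create the randomization sequence".

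Four other sections bear on the point:

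- **Recruitment:** 44 people are drawn first, and "subsequently, they will be randomized into the study groups: placebo and ω3".
- **Assessments to randomization:** anthropometry, body composition and eleven blood measures are taken before allocation.
- **Blinding:** a local pharmacy labels identical containers with codes.
- **Data treatment and statistical aspects:** a two-way analysis of variance with time, treatment and covariates comes first; anthropometric and blood variables are among the examples of covariates. For Student's t and Mann-Whitney, the section then says that the "test will be used to investigate group differences (placebo and treatment").

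**The concern.** The envelope step reads as a complete allocation. The sort-and-pair step that follows is also an allocation, because its stated action is to place participants in groups. Its stated aim is similarity of the groups on measured values. Nothing says that the computer sequence, or any other chance device, decides which member of a pair goes to which arm. The sorting variables are not named, and neither is the person who sorts and allocates.

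The stake is the inference itself. A between-group p-value in a trial of 44 people takes its justification from the random assignment. If a rule or a person working from baseline values fixes the arm, that justification is gone, and the allocation cannot be reproduced or audited from the text.

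**Working it through.** **1. Can both steps fix the arm?** The allocation paragraph gives no figure to reproduce, so the statements are set side by side.

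- If the envelope number fixes the arm, the later grouping either changes it or does nothing.
- If the envelope number does not fix the arm, the text never says what it decides.
- The sort-and-pair step is placed after the envelopes, so on a literal reading it is the one that counts.
- The later mention of the data manager's sequence does not say that the sequence is applied inside the pairs.
- Recruitment, Procedures and Blinding refer only to randomisation or to coded containers. None of them links the two steps.

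**2. Is a value-driven allocation feasible as described?** Yes. All 44 are drawn before allocation, and their baseline values are already known.

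**3. How many allocations are possible?** Inputs: 44 participants, 22 per arm, hence 44/2 = 22 pairs.

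| Procedure | Possible allocations |
|---|---|
| Fixed rule on sorted pairs | 1 |
| Chance within each pair | 2^22 = 4,194,304 |
| Unrestricted 22:22 | C(44,22) ≈ 2.1 × 10^12 |

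With only one possible allocation there is no randomisation distribution to test against.

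**4. How large is the imbalance on the sorting variable?** Assumption: one normally distributed sorting variable. In 100,000 simulated sets, 44 standard normal values were sorted and paired with their neighbours.

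- Lower member always to the same arm: mean difference 0.112 SD (range 0.03 to 0.29), always in the same direction.
- Chance within pairs: mean difference 0.00, SD 0.04.
- For comparison, unrestricted 22:22 randomisation gives a chance difference with SD of about sqrt(2/22) = 0.30.

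If the sorting variable correlated 0.5 with the outcome (assumed), 0.112 SD would carry over as 0.5 × 0.112 = 0.056 SD. The planned effect size is d = 1.15.

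**5. What happens if pairs are formed and the test ignores them?** With close matching on a variable that correlates r with the outcome, the unpaired standard error is too large by a factor of 1/sqrt(1 − r²). The documents give no r, so a range is shown.

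| Assumed r | 1/sqrt(1 − r²) | SE overstated by |
|---|---|---|
| 0.2 | 1/sqrt(0.96) = 1.02 | 2% |
| 0.3 | 1/sqrt(0.91) = 1.05 | 5% |
| 0.5 | 1/sqrt(0.75) = 1.15 | 15% |

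The error is in the conservative direction: power is lost and false positives are not added.

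**The case against.** The strongest reply is that this is matched-pair randomisation described out of order. The section asserts random assignment, gives a 1:1 generated sequence and ends with an independent person creating it. Blocks of two fit that design, and a condensed article may omit the mechanics. This stands as a plausible reading of intent. It does not remove the defect, because the article does describe a mechanism, and the mechanism conflicts with itself on which step sets the arm.

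A reader might also draw stronger conclusions that the documents do not support:

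- **That the trial was not randomised.** The text neither states nor excludes chance within pairs. The finding concerns the written procedure, not what was done.
- **That concealment is lost.** All 44 are drawn before allocation, so foreknowledge of an assignment cannot steer who enters. Who performs the pairing is not stated, and the only person named is outside clinical practice and recruitment. Sorting on patient values is not itself a fault; pair matching requires it.
- **That the imbalance has no limit.** When adjacent pairs are split one per arm, the mean within-pair gap is the limit on the sorting variable. Only variables outside the sort are left open to discretion.
- **That several variables cannot be put in one order.** A nested sort or a composite score does so. The gap is that neither the variables nor the rule is named.
- **That the analysis ignores the pairing altogether.** The first-listed model allows anthropometric and blood covariates, which could absorb it. Only the unpaired t and Mann-Whitney tests clearly ignore it.

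**Conclusion.** The concern holds as a defect in the written allocation procedure. Two steps are given, they cannot both determine the arm, and no chance element is stated for the later one. Taken literally, the final assignment follows patient values and is not random.

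The likely numerical bias is small: about 0.11 SD on the sorting variable under the fixed rule that favours one direction most, assuming a single normally distributed variable and adjacent pairs split one per arm. That is below the ordinary chance imbalance of simple 22:22 randomisation, although it always points the same way. The weight of the point lies in the lost random basis for every between-group test and in the discretion left open. The effect on the unpaired tests is secondary and depends wholly on the assumed correlation.

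**What to change.** Replace the paragraph with one procedure:

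1. Name the sorting variable in advance, or the composite score and its formula.
2. Once all 44 are assessed, the independent data manager sorts them and forms 22 pairs.
3. The SPSS random sequence, with its seed archived, decides which member of each pair receives which coded arm.
4. The envelope or pharmacy code only carries that assignment and does not generate it.

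In the statistical section, put the sorting variable (or the pair) into the between-group model already planned with covariates, and base the group comparison on that model rather than on the unpaired t or Mann-Whitney test. The sorting variable is the more practical choice. At the assumed 40% dropout, if losses are independent within pairs, only about 22 × 0.6² ≈ 8 pairs would stay complete.

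If allocation has already taken place, report exactly what was done: which variables were used, who sorted, and what decided the arm within each pair.

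The cost is one rewritten paragraph, one sentence in the analysis section and a short script for the data manager already named. No patients or visits are added.
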